## Abstract

**Background:** Neonatal deaths, estimated at approximately 4 million annually, now account for almost 40 % of global mortality in children aged under-five. Bacterial sepsis is a leading cause of neonatal mortality. Assuming the mother is the main source for bacterial transmission to newborns, the primary objective of the trial is to determine the impact of one oral dose of azithromycin, given to women in labour, on the newborn's bacterial carriage in the nasopharynx. Secondary objectives include the impact of the intervention on bacterial colonization in the baby and the mother during the first month of life.

**Methods/design:** This is a Phase III, double-blind, placebo controlled randomized clinical trial in which 830 women in labour were randomized to either a single dose of 2 g oral azithromycin or placebo (ratio 1:1). The trial included pregnant women in labour aged 18 to 45 years attending study health centres in the Western Gambia. A post-natal check of the mother and baby was conducted at the health centre by study clinicians before discharge and 8–10 days after delivery. Home follow up visits were conducted daily during the first week and then weekly until week 8 after delivery. Vaginal swabs and breast milk samples were collected from the mothers, and the pathogens *Streptococcus pneumoniae*, *Group B Streptococcus* (GBS) and *Staphylococcus aureus* were isolated from the study samples. For bacterial isolates, susceptibility pattern to azithromycin was determined using disk diffusion and E-test. Eye swabs were collected from newborns with eye discharge during the follow up period, and Chlamydial infection was assessed using molecular methods.

**Discussion:** This is a proof-of-concept study to assess the impact of antibiotic preventive treatment of women during labour on bacterial infections in the newborn. If the trial confirms this hypothesis, the next step will be to assess the impact of this intervention on neonatal sepsis. The proposed intervention should be easily implementable in developing countries.

**Trial registration:** ClinicalTrials.gov Identifier -NCT01800942- First received: February 26, 2013.

**Keywords:** Bacterial colonization, Neonatal sepsis, Azithromycin, Randomized clinical trial, Sub-Saharan Africa

\* Correspondence: [contact]

 Medical Research Council Unit, Fajara, The Gambia

 London School of Hygiene and Tropical Medicine, London, United Kingdom

Full list of author information is available at the end of the article

## Background

The last decade witnessed a substantial reduction in the risk of under-five child mortality [1–3]. However, the greatest reduction occurred in children older than 1 month. Neonatal deaths, estimated at approximately 4 million annually, now account for almost 40 % of the world's deaths in children under-five [4] with approximately 75 % of these deaths occurring during the first week of life [5]. The highest rates of mortality in this age group occur in Sub-Saharan Africa (SSA).

Invasive bacterial disease, which mainly presents as sepsis, is estimated to cause one out of three deaths in this age group [5]. In the African continent, neonatal sepsis is caused by a wide range of bacterial pathogens [6] that differ between the early (first week of life) and late (days 8 to 28) neonatal period. During the early neonatal period, when most neonatal sepsis occur [7], gram positive bacteria predominate among sepsis case with *Staphylococcus aureus* [5] and *Streptococcus pneumoniae* being the most frequently bacteria isolated, closely followed by group B *Streptococcus* (GBS) [6].

Vertical transmission from the mother plays an important role in early neonatal sepsis. Newborns may be infected during labour as they pass through the birth canal, or during the first hours/days of life through close physical contact with the mother, if, as is commonly the case in SSA, the mother carries pathogenic bacteria in the nasopharyngeal tract or breast milk [5, 8–10].

Azithromycin (AZI) is a macrolide with a wide antimicrobial spectrum; it is effective against organisms such as macrolide-susceptible *Staphylococcus* species and *Streptococcus* species [11]. AZI is currently licensed for use in infants aged >6 months and is used to treat a wide range of infections, including those occurring during pregnancy [12, 13]. Data on the effect of treating pregnant women with up to 2 g of AZI for prevention of malaria and preterm birth are available [12–16]. Although scarce information exists, AZI appears to be excreted in human milk at a very low concentration [17]. According to a case report, an infant who is exclusively breastfed would receive approximately 1/10 or 1/20 of the dose recommended in infants ≥6 months old [18]. Thus far, there are limited safety data on AZI in neonates. Two trials among hospitalized neonates (one including 111 low birth weight neonates admitted to hospital and the other involved 2400 infants including neonates) have not shown severe adverse reactions [19, 20]. In another published study, AZI was given to 58 newborns as prophylaxis for pertussis [17] and only mild gastrointestinal adverse reactions were observed [16]. No additional adverse events were observed in the same study among newborns from AZI treated mothers [17].

Orally administered AZI is widely distributed throughout the body. In pregnant women, after one oral dose,

peak plasma concentrations are attained within 6 h; myometrium concentrations reach high levels within this time [21]. The elimination half-life from plasma and tissues is 2–4 days. Some published literature show adverse reactions (i.e. gastrointestinal, headache) or allergic reactions (i.e. rash or swelling).

As part of the WHO-recommended trachoma control strategy, mass AZI treatment campaigns have been carried out in several trachoma endemic countries [22, 23], including The Gambia [24]. The additional benefits of these campaigns include decreased nasopharyngeal bacterial carriage [25], and childhood morbidity and mortality [26].

In The Gambia, the prevalence of AZI resistance after these mass AZI treatment campaigns was very low. For example, among *S.pneumoniae* isolates collected 6 to 30 months after treatment, resistance ranged between 0.3 and 0.9 % [25]. The relevance of acquired macrolide resistance for bacterial infections is uncertain but likely to be minimal in settings like the Gambia (and other African countries) where macrolides are very rarely used as empirical antibiotic therapy. In addition, there is evidence elsewhere from patients with cystic fibrosis receiving long term AZI, that although macrolide resistance develops in *S. aureus* among treated patients, these resistant organisms are not transmitted to their close family contacts [27].

New interventions to decrease neonatal mortality are urgently needed. If the mother is an important source of bacterial transmission to the newborn, then an intervention that reduces bacterial infections in the mother may prevent bacterial transmission and neonatal sepsis. In this study, we evaluate the impact of one oral dose of AZI given during labour on the asymptomatic bacterial carriage in the newborn baby as well as the mother. If successful, this simple intervention could be easily implemented at even the most remote health facilities. It has the potential to achieve wide coverage in SSA where low-cost interventions to reduce neonatal mortality are urgently needed.

## Methods/design

### Study objectives

The primary objective of the trial is to determine the impact of one oral dose of 2 g of AZI, given during labour, on the newborn's nasopharyngeal bacterial carriage at the age of 6 days for at least one of three pathogens: *S.aureus*, GBS and *S. pneumoniae*.

Secondary objectives are to determine the impact of the intervention on bacterial carriage in the nasopharynx of the baby, and in the vaginal tract and breast milk of the mother at different time points within the first 4 weeks after delivery. The impact of AZI on purulent conjunctivitis and ocular *C. trachomatis* infection will also be assessed.

To evaluate the safety of the intervention on mothers and newborns we monitored and assessed adverse events (AE). Special attention was paid to hypertrophic pyloric stenosis (HPS) in the newborn which is usually reported as projectile vomiting.

### Study endpoints

The primary endpoint is the prevalence of nasopharyngeal carriage of the newborn at the age of 6 days for any of the following bacteria: *S.aureus*, GBS and *S.pneumoniae*.

Secondary endpoints include:

- Prevalence of nasopharyngeal bacterial (*S.aureus*, GBS and *S.pneumoniae*) carriage of the newborn at different time-points during the first months of life.
- Prevalence of nasopharyngeal, vaginal and breast milk bacterial carriage (*S.aureus*, GBS and *S.pneumoniae*) of the mother at different time-points during the first month after delivery.
- Prevalence of non-susceptibility to macrolides among bacteria (*S.aureus*, GBS and *S. pneumoniae*) isolated from the clinical samples collected from the newborns and their mothers during the first month after delivery.
- Proportion of newborns with at least one episode of purulent conjunctivitis and ocular *C. trachomatis* infection within the first week of life, the first 4 weeks of life and during the 8 weeks of the follow-up period.

We also measured AZI concentrations in the breast milk of the first 40 women recruited into the trial at two time points during the first week of life. Other endpoints not initially included in the protocol are weight gain during the first 8 days of life and the time from BCG vaccination to the appearance of a scar.

As safety endpoints, we included the number of solicited and unsolicited AEs in mothers and newborns observed during the first 6 days after treatment; and number of AEs in mothers and newborns reported during the first 8 weeks after treatment.

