### **Sample size rationale**

The original sample size (415 mother/baby pairs per arm) assumed a 15 % loss to follow-up (i.e. 353 participants in each arm for whom the primary endpoint is recorded). Based on data from a previous study [32], bacterial carriage (*S.aureus*, GBS or *S.pneumoniae*) on day 6 was assumed to be 60 % in the control arm. According to these assumptions, the study has 98 % power to detect a 25 % reduction in bacterial carriage (GBS, *S.pneumoniae* or *S.aureus*) and 88 % power to detect a 20 % reduction.

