screening programmes are difficult to implement in SSA and other developing regions. Still, screening may not be needed where at least half of pregnant women are vaginal carriers of one of the most common bacteria associated with neonatal sepsis [35]. In Africa, other known risk factors for early neonatal sepsis, such as preterm or low birth weight [7] and premature rupture of membranes or prolonged labour [36], are also common.

The relevance of acquired macrolide resistance for outcome of episodes of clinical infection is uncertain, but is likely to be minimal in a setting like the Gambia and other African countries where macrolides are very rarely used as empirical antibiotic therapy. Also, previous studies in The Gambia show that after mass AZI campaigns for trachoma control, prevalence of AZI resistance among *S.pneumoniae* isolates was re-established to baseline levels (<1 %) [25]. In addition, there is evidence elsewhere from patients with cystic fibrosis receiving long term AZI, that although macrolide resistance develops in *S. aureus* among treated patients, these resistant organisms are not transmitted to their close family contacts [27].

In this proof-of-concept study, we propose an intervention that would be easily implementable in developing countries. We treat women in labour attending a health facility with one dose of AZI, an oral antibiotic that is cheap and does not need specific storage conditions (can be kept at room temperature), and we will assess whether this antibiotic decreases the risk of bacterial colonization in the baby during the neonatal period (primary endpoint during the first week of life or early neonatal period) and the mother during the same period. The hypothesis that motivates our intervention is that the mother is the main source of bacterial transmission to the baby. If the intervention is successful in proving our hypothesis, then we will design several additional studies. First, we will assess the impact of the intervention on severe clinical endpoints such as neonatal sepsis and mortality in the baby and puerperal sepsis in the mother. If this is shown to be of benefit, we will then test the intervention in the context of home delivery, as in Africa, many women deliver at home attended by traditional birth attendants.

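### The macrolide-resistance endpoint is a share of isolates, a denominator azithromycin is expected to shrink, so comparing that share between arms is not a randomised comparison

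*Protocol*

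**What the plan says.** Protocol, Study endpoints, lists as a secondary endpoint "Prevalence of non-susceptibility to macrolides among bacteria" of the three study species, "isolated from the clinical samples collected from the newborns and their mothers during the first month after delivery". The denominator is what the laboratory recovered. The two carriage endpoints listed just before it are prevalences in newborns and in mothers.

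The Background says of azithromycin that "it is effective against organisms such as macrolide-susceptible" staphylococci and streptococci. The primary objective is to reduce newborn carriage of the same three species whose isolates form the resistance denominator.

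The Sample size rationale sets the expected fall. Carriage of any of the three species "on day 6 was assumed to be 60 % in the control arm", with "98 % power to detect a 25 % reduction in bacterial carriage" and "88 % power to detect a 20 % reduction", on "353 participants in each arm for whom the primary endpoint is recorded".

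The Statistical analysis section plans carriage prevalence by arm, species and time point, with prevalence ratios and 95% confidence intervals. It does not mention resistance. The Antibiotic susceptibility testing section covers only laboratory classification. Nowhere does the protocol define a resistance measure per sampled mother or newborn.

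**The concern.** Having an isolate to test is itself an outcome measured after randomisation, and it is the outcome the drug is meant to reduce. The reduction should fall mainly on susceptible strains. The isolates in the two arms are then differently selected sets, and a comparison of their resistant shares loses the protection of randomisation.

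A higher share in the azithromycin arm could mean that more people carry resistant strains. It could also mean that the same number do, while susceptible strains have been cleared around them. The share alone cannot tell these apart. The more effective the drug, the larger the apparent rise in resistance. A reader who wants to know whether the intervention puts more resistant bacteria into newborns and mothers needs the count per person sampled.

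**Working it through.** **Inputs from the protocol.** Control carriage 60%, relative reductions of 20% and 25%, and 353 evaluable per arm (Sample size rationale). Resistance of 0.3 to 0.9% among *S. pneumoniae* isolates after mass treatment (Background). Fisher's exact test for comparisons of prevalence (Statistical analysis). No significance level is stated; two-sided 5% is assumed, in line with the 95% intervals.

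**The plan's own figures.** 415 × 0.85 = 352.75, i.e. 353. The planned reductions are relative: 0.60 × 0.80 = 0.48 and 0.60 × 0.75 = 0.45. The normal approximation for two proportions with 353 per arm gives 98.0% power for 60% against 45% and 89.4% for 60% against 48%. With a continuity correction these are 97.6% and 87.9%. The stated 98% and 88% are reproduced, so the carriage figures can be used as they stand.

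**The identity.** Let *C* be carriage prevalence, *R* the proportion of all sampled newborns carrying a resistant strain, and *d* the relative reduction in carriage. With one isolate per carrier, the share among isolates is *R/C*. Hold *R* equal in both arms and let the drug remove only susceptible carriage:

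- control share = *R*/0.60
- azithromycin share = *R*/[0.60 × (1 − *d*)]
- ratio = 1/(1 − *d*), whatever the value of *R*

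This is 1/0.80 = 1.25 at *d* = 20% and 1/0.75 = 1.33 at *d* = 25%. Over all sampled newborns the ratio is *R/R* = 1.00.

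**Numbers put in.** The row with *R* = 5% is an assumption for illustration. The 0.3% and 0.9% rows take the Background range as the control share.

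| | Control (60%) | 20% reduction (48%) | 25% reduction (45%) |
|---|---|---|---|
| Carriers among 353 | 212 | 169 | 159 |
| Share, *R* = 5% (17.7 per arm) | 8.3% | 10.4% | 11.1% |
| Share, control 0.3% | 0.30% | 0.38% | 0.40% |
| Share, control 0.9% | 0.90% | 1.13% | 1.20% |

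In the last two rows the shift runs from 0.08 (0.375 − 0.30) to 0.30 (1.20 − 0.90) percentage points.

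**Effect on a test.** A simulation with 1,500 runs per scenario, one isolate per carrier and *R* equal in both arms gave the rejection rates of Fisher's exact test below. The protocol does not say that this test will be applied to the resistance share; the table shows what would follow if it were. The values of *R* are assumptions.

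| *R* (share of control isolates) | On isolates, 20% / 25% reduction | On all sampled, 20% / 25% reduction |
|---|---|---|
| 2% (3.3%) | 5.4% / 6.2% | 2.7% / 2.7% |
| 5% (8.3%) | 10.1% / 12.4% | 4.2% / 3.8% |
| 10% (16.7%) | 19.1% / 23.9% | 4.2% / 4.3% |

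The simulation standard error near 5% is √(0.05 × 0.95/1500) = 0.6 percentage points. The isolate-based rates at *R* = 2% are therefore close to nominal, and those at 5% and 10% are clearly above it.

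**The case against.** **The protocol names an endpoint and does not say how arms will be compared on it.** This stands, and it is why the point is conditional on a between-arm comparison of the share. A reader might also infer that repeat isolates from one person will be counted as independent, across species, sites and visits. The protocol does not say so. Their handling may be settled in a statistical analysis plan that is not at hand, so it is no part of this point.

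**Carriage will be reported beside the share.** This stands in part. For one species, site and time point, with one isolate tested per positive sample, carriage times share recovers the per-person figure: 0.60 × 8.33% = 5.0% and 0.45 × 11.11% = 5.0%. That gives a point estimate but no interval for the ratio, and it fails once the share is pooled over species, sites or times.

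**At the only resistance figures given, the effect is negligible.** This stands for *S. pneumoniae*. At 0.9% of 212 control isolates about 1.9 resistant isolates are expected, and no test would call a shift on that scale a signal. Clear inflation of the error rate needs a control share of about 8.3%, roughly nine times 0.9%. The protocol gives no figure for *S. aureus* or GBS, so it neither supports nor excludes such a level.

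**The planned reductions concern newborn nasopharyngeal carriage at day 6, any species.** This stands. Carrying 20 to 25% over to mothers, vaginal swabs, breast milk, single species or the rest of the month is extrapolation.

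**The share among isolates is a legitimate measure.** This stands. It describes the flora that remains and matches the form in which the Background quotes earlier Gambian resistance data. It should be kept.

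**Resistance might be read as the trial's main harm question.** The documents do not support that. The stated safety objective is adverse events, with special attention to pyloric stenosis in the newborn, and the Background and Discussion call the relevance of acquired macrolide resistance uncertain and probably minimal in this setting. The Discussion's remark on resistance after mass campaigns is background from an earlier survey, not a second instance of the problem.

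**Conclusion.** The point holds in a limited form. The endpoint as worded uses a denominator that treatment is expected to change, and the protocol offers no per-person alternative. If the share is compared between arms, it is inflated by 1.25 to 1.33 at the planned 20 to 25% reductions with no extra resistant carrier.

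This rests on three assumptions: resistant carriage is equal in the two arms, the drug removes only susceptible carriage, and each carrier yields one isolate. Where carriage does not fall, there is no artefact. In absolute terms the shift is about 0.1 to 0.3 percentage points at the resistance quoted for *S. pneumoniae*, and larger only if resistance is commoner in the other two species.

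A reader might go further and conclude that the trial is bound to report a false resistance signal. That does not follow: no test of this share is specified, and at the quoted resistance levels the distortion would be too small to detect. The primary endpoint is not affected.

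**What to change.** Make the between-arm comparison the proportion of all sampled newborns, and separately of all sampled mothers, who carry at least one azithromycin non-susceptible isolate. Give it per species and combined, at each time point, with a prevalence ratio and 95% confidence interval as already planned for carriage.

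Keep the share among isolates beside it, with numerators and denominators, labelled as a description of the remaining flora.

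The cost is one added table and percentages that look smaller. The laboratory data are the same. Trial status reports laboratory work and data cleaning as still ongoing, and Blinding and Un-blinding says the code is broken only after database lock, so on the protocol's account the comparison can be fixed before allocation is known.

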### Health centre discharge, follow up and sampling (Table 1 and Fig. 3)

Women were kept under close observation by study nurses. The JFPH nurses conducted the delivery. When the baby was born, the study nurse on duty collected the NPS within 6 h of birth. A clinical examination of both mother and baby were carried out by one of the study clinicians before discharge (Table 1), which occurred 6 to 24 h (mostly within 6–10 h) after delivery if both were clinically stable and there were no serious adverse events (SAE). Then, participants were given a Participant Identification (ID) card for further identification.

Home visits were conducted for each mother/baby pair for 8 weeks. In the first week, a nurse followed-up both mother and baby with daily recording of information on the health status of the pair and any adverse events (AE). During this week, samples were collected on days 3 and 6, including NPS from mother and baby and breast milk from the mother (Table 1).

Between the 8 and 10 days after the delivery, both mother and baby presented at the study site where the research clinician evaluated them and a vaginal swab was collected from the mother (Table 1). At that point, the babies presented at the infant welfare clinic to receive their BCG, OPVo, and Hepatitis B vaccines.

During the next 7 weeks, a field worker followed up the mother/baby pair. At weeks 2 and 4, breast milk samples were collected from the mothers and NPS from both mothers and babies (Table 1). If the baby was noted to have eye discharge during any of the visits, an eye swab was collected and clinical information recorded. Treatment was given appropriately.

In the advent of any symptoms or signs of illness during home visits, the field worker called the nurse coordinator who, if necessary, asked the mother and baby to go to the study site to be assessed by the nurse coordinator or his assistant or when indicated, by the study clinicians.

If during the follow-up period, either mother or baby needed antibiotics, samples were collected in lieu of the next scheduled sample and participants were started on antibiotics. If a mother was on antibiotics, no more samples were collected from her or the baby. If the baby was on antibiotics, subsequent samples were still collected from the mother.

**Table 1** Summary of the study activities including follow up visits and sampling

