A Poisson regression model will be used to assess the effect of the intervention on prevalence of carriage across all time points. The model will include time, baseline carriage status of the mother, mother's age, ethnicity, season, sex of the newborn, and gestational age. Robust standard errors will be used to account for the dependence between observations from the same individual as well as the model misspecification (carriage status is binary and therefore does not follow a Poisson distribution).

To calculate prevalence of carriage at day 3 and day 6 we will use data from samples (NPS newborns and mothers, breast milk) collected within 1 day of the scheduled visit. At 14 days we will use samples collected between 12 and 18 days, and at 28 days we will use samples collected between 25 and 31 days. For vaginal bacterial carriage at day 8–10 we will use samples collected between 7 and 13 days. Samples were not collected after children received antibiotics. Where a sample was collected in lieu of the missing sample (i.e., before antibiotics were given) this will be used in place of the missing sample, even if it was collected outside the appropriate window period.

We will present analyses based on the available data. For the primary outcome we will conduct two additional analyses using the ITT cohort. First, a subgroup analysis in women who gave birth 2 h or more after taking the drug. And second, a sensitivity analysis using multiple imputation of missing data. In the imputation model, bacterial carriage in missing samples will be imputed from data on bacterial carriage at other time points and baseline demographic data (age and ethnicity for mothers, and sex and birth weight for newborns).

Changes in prevalence of bacterial carriage over time will be plotted for NPS in mothers and newborns, and breast milk. The plots will include point-wise 95 % confidence intervals for each prevalence estimate.

The numbers and rates of adverse events, serious adverse events (overall and specifically with a diagnosis of neonatal sepsis), purulent conjunctivitis, Chlamydial conjunctivitis, and deaths in newborns will be reported by trial arm. Rates of adverse events and serious adverse events will be reported in mothers. Rates will be compared between trial arms using Poisson regression, and robust standard errors will be used to allow for heterogeneity in the rates between individuals.

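### Conjunctivitis is declared as a per-infant proportion at 1, 4 and 8 weeks, but the stated analysis compares rates without that definition or those windows

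*Protocol*

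**What the plan says.** Protocol, Study endpoints, gives as a secondary endpoint the "Proportion of newborns with at least one episode of purulent conjunctivitis and ocular" disease due to *C. trachomatis*. The unit is the infant, the outcome is yes or no, and there are three cumulative windows, ending at 1, 4 and 8 weeks. The Study objectives section lists the effect on these two conditions with the secondary objectives, in a different paragraph from safety.

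Protocol, Statistical analysis, deals with conjunctivitis only in its last paragraph. There, "The numbers and rates of adverse events, serious adverse events" and, in the same list, "purulent conjunctivitis, Chlamydial conjunctivitis, and deaths in newborns will be reported by trial arm". The comparison is stated next: "Rates will be compared between trial arms using Poisson regression". On the variance, the text adds that "robust standard errors will be used to allow for heterogeneity in the rates between individuals".

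The ratio of prevalence with 95% CI and Fisher's exact test, described earlier in that section, are stated for the comparisons of carriage.

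On data capture, the section on discharge, follow-up and sampling says: "If the baby was noted to have eye discharge during any of the visits, an eye swab was collected". Visits are daily in the first week and weekly from then to week 8.

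**The concern.** The endpoint collapses any number of episodes in an infant to a single yes. A rate, in the ordinary sense, is a count of events over time at risk, so an infant with two episodes contributes twice. These are different quantities, and the protocol declares one while naming a method for the other.

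The protocol gives no rule for separating a new episode from a continuing one, and eye discharge is looked for at every visit. If events are taken from visit records, discharge that lasts several days in week 1 could enter more than once. The estimate would then mix two effects: whether azithromycin prevents conjunctivitis, and whether it changes how long conjunctivitis lasts or how often it recurs.

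At stake is the reading of one secondary efficacy endpoint. Two analyses could each be defended from the protocol's text, and they need not agree. The primary endpoint and the sample size are not affected.

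**Working it through.** **Text comparison.** The protocol has no conjunctivitis figure to reproduce, so the first step sets the two sections side by side.

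| Feature | Study endpoints | Statistical analysis |
|---|---|---|
| Measure | Proportion of infants | Numbers and rates |
| Repeats | Collapsed to yes/no | Not addressed |
| Windows | 1, 4 and 8 weeks | None named |
| Method | None named | Poisson regression, robust errors for varying individual rates |

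The reason given for robust errors is informative. For the carriage model, the same section says that carriage is binary and that robust errors are needed partly because the Poisson form is therefore wrong. For the paragraph containing conjunctivitis, the reason is that rates differ between individuals. That reason fits counts per infant better than a yes/no outcome.

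**Relation between the two measures.** Let p be the proportion of infants ever affected and m the mean number of counted events per affected infant, with subscript 0 for control and 1 for azithromycin. With equal follow-up in the arms:

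- proportion ratio = p1 / p0
- rate ratio = (p1 × m1) / (p0 × m0) = proportion ratio × (m1 / m0)

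The two are equal only when m1 = m0.

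**Illustration.** All values of p and m below are assumptions.

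With p0 = 0.20 and p1 = 0.16, the proportion ratio is 0.16 / 0.20 = 0.80.

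- m0 = m1: rate ratio = 0.80, no difference between the measures.
- m0 = 3, m1 = 2: (0.16 × 2) / (0.20 × 3) = 0.32 / 0.60 = 0.53.
- m0 = 2, m1 = 3: (0.16 × 3) / (0.20 × 2) = 0.48 / 0.40 = 1.20.

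With p0 = 0.20 and p1 = 0.12, the proportion ratio is 0.12 / 0.20 = 0.60.

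- m0 = m1 = 1.5: 0.18 / 0.30 = 0.60.
- m0 = 1.5, m1 = 1.2: 0.144 / 0.30 = 0.48.
- m0 = 1.2, m1 = 1.5: 0.18 / 0.24 = 0.75.
- m0 = 2.0, m1 = 1.0: 0.12 / 0.40 = 0.30.

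The gap can go in either direction, and it vanishes when counts per affected infant are equal.

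**The case against.** The strongest reply is that the Poisson wording does not force repeat counting. The same list includes deaths in newborns, which can occur only once per infant, so the paragraph already covers outcomes of the yes/no kind. The protocol also uses Poisson regression with robust errors for carriage, which it recognises as binary. Applied to an infant ever having had an episode, that model estimates a proportion ratio, which is what the endpoint asks for. This stands as a possible reading. It does not remove the mismatch, because the paragraph states neither the per-infant outcome nor the windows, and its reason for robust errors points towards counts.

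A reader might infer more than the text supports on four points:

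- **That every visit record will be counted as an event.** The protocol says only that discharge leads to a swab and recorded clinical information. Repeat counting is possible under the stated model but is not declared.
- **That conjunctivitis has no planned comparison between arms.** It has one, but on rates.
- **That more frequent visits in week 1 distort the ratio on their own.** The schedule is the same in both arms of a double-blind trial. A distortion needs duration or recurrence to differ between arms.
- **That the word joining the two conditions requires both to be present.** The analysis paragraph names them separately, so the intent is clear enough.

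It can also be said that windows and episode rules are commonly left to an SAP. That is fair for the episode rule. It does not cover a case where the protocol itself names a method that, read plainly, targets another quantity.

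**Conclusion.** The point holds as a mismatch between a declared secondary endpoint and its stated analysis. Study endpoints asks for the proportion of infants ever affected by 1, 4 and 8 weeks. Statistical analysis, read as written, gives a comparison of rates that can include repeats and names no window.

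The size cannot be estimated from the protocol, which gives no frequency, duration or recurrence of conjunctivitis. Under the assumed 20% and 16%, the rate ratio runs from no discrepancy (0.80) to 0.53 with 3 and 2 counts per affected infant. The whole of that shift comes from the assumed difference in counts, so 0.53 shows what is possible and is not a forecast. If few infants have more than one counted event, the two measures will be close.

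The matter should be corrected, but it is not critical: it concerns one secondary endpoint.

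**What to change.** In Statistical analysis, state that purulent conjunctivitis and *C. trachomatis*-positive conjunctivitis are each analysed as a per-infant yes/no outcome (at least one episode) by 1, 4 and 8 weeks. Report a risk ratio with 95% CI for each window, either by the method already given for carriage prevalence or by Poisson regression with robust errors on the binary outcome.

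Take as the denominator the infants followed through the window in question, with a sensitivity analysis for those lost earlier. Placing all live-born infants in the denominator without such a rule would treat infants lost before the end of a window as free of the condition. The sample size section itself allows for 15% loss in recording the primary endpoint.

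The event rate may remain as a supplementary safety summary, preferably with a sentence saying what counts as a new episode.

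The cost is a wording change and one derived variable per condition and window, from data already collected. The Trial status section reports laboratory work and data cleaning as still in progress, and Blinding and Un-blinding says the code is broken only after database lock, so the choice can be fixed while allocation is concealed.
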